## Abstract

**Background:**

Respiratory impairments refer to a reduction in pulmonary function, which may adversely affect an individual’s health. Incentive spirometry is a technique designed to assist patients in achieving a pre-set airflow volume; the volume is determined from predicted values or baseline measurements. Our study aims to assess the effect of incentive spirometry on respiratory impairments.

**Method:**

Fifty-four patients aged 40 years and above with obstructive, restrictive or mixed respiratory impairments attending the respiratory clinic at the Lagos State University Teaching Hospital, Ikeja (LASUTH), will be recruited and assigned to three groups of 18 participants based on the class of respiratory impairment. Participants in each category of respiratory impairment will be subdivided into three groups. A final group of six participants per class of impairment will participate in the experiment. Our study will be a double-blind, randomised control trial with two intervention groups and one parallel placebo control group. Pulmonary function will be assessed before and after every procedure while the six-minute walk test (6MWT), Medical Research Council dyspnoea scale and the Pulmonary Functional Status and Dyspnea Questionnaire-Modified will be assessed fortnightly during our study. Data will be analysed using descriptive and inferential statistics and a repeated MANOVA; *p* < 0.05.

**Discussion:**

The outcome of our study may reveal the effect of inspiratory and expiratory incentive spirometry on obstructive, restrictive or mixed respiratory impairments.

**Conclusion:**

Our study may contribute to the body of knowledge on pulmonary rehabilitation.

**Clinical implication:**

Our study results may indicate if inspiratory incentive spirometry or expiratory incentive spirometry is better suited for the treatment of the respiratory impairment.

**Trial Registration:**

www.pactr.org: PACTR202005904039357

## Background

Respiratory impairment is a common condition seen by healthcare service providers in primary healthcare, pulmonary medicine and other specialties. It is more common in older persons and the aging population (Vaz Fragoso & Gill 2012).

Respiratory diseases may lead to a significant reduction in the timed lung volume; the forced expiratory volume in 1 sec to forced vital capacity ratio (FEV_1_/FVC) is reduced and defines airflow limitations because of airway obstruction (Pellegrino et al. 2005). Respiratory diseases that lead to comparable reductions in the timed and untimed lung volumes include those that affect the chest wall and respiratory muscles, leading to a normal FEV_1_/FVC but reduced FVC (Pellegrino et al. 2005).

According to Fletcher (2019), respiratory symptoms such as dyspnoea have been found in a quarter to a third of the adult population with respiratory conditions such as chronic obstructive pulmonary disease (COPD). Chronic obstructive pulmonary disease is a group of progressive lung diseases commonly associated with emphysema, chronic bronchitis or both and are also associated with adverse outcomes such as increased disability and increased risk of death in the aging population (Agusti 2005; Soriano et al. 2005). Emphysema can lead to airway obstruction following the destruction of air sacs, while mucus build-up from inflammation can occur in bronchitis (Agusti 2005; Soriano et al. 2005).

Cystic fibrosis and idiopathic pulmonary fibrosis (IPF) are classified as restrictive airway diseases characterised by scarring of the lung tissues leading to a progressive decline in lung function (Liao et al. 2017). Interstitial lung disease (ILD) manifests as inflammatory, fibrotic infiltration of the alveolar walls resulting in the loss of lung tissue wall compliance (Nwosu et al. 2020). According to Anyabolu et al. (2013), the prevalence of IPF in the United States is 14 per 100 000; however, a scarcity of data is seen in the Nigerian population. A retrospective study between January 2015 and October 2018 by Nwosu et al. (2020) revealed that ILD accounted for 2.3% of respiratory conditions.

Diagnosis of respiratory diseases is frequently established through spirometry because pathological confirmation is invasive and not routinely available. Hence, airflow obstruction or restrictive patterns collectively referred to as respiratory impairment is often detected through spirometry (Marcus et al. 2015). In summary, respiratory conditions such as asthma and COPD are classified as obstructive diseases, while those involving the chest wall, respiratory muscles, pleura or lung parenchyma are considered restrictive in nature (Vaz Fragoso & Gill 2012).

The diagnostic criteria that define spirometry respiratory impairment are often based on the Global Initiative for Obstructive Lung Disease (GOLD) (Quanjer et al. 1993). The threshold of < 0.70 for the spirometry ratio of FEV_1_ to FVC classifies normal spirometry, airflow obstruction or restriction in the adult population (Leivseth et al. 2013, Quanjer et al. 1993, Vaz Fragoso & Gill 2012). Airway obstruction is defined with an FEV_1_/FVC ratio of < 70% and an FVC of > 80% predicted, FEV_1_/FVC ratio of > 70% and an FVC of < 80% predicted for restrictive defects, while mixed defects are identified with FVC of < 80% predicted and an FEV_1_/FVC ratio of < 70% (Mathew et al. 2016; Uzma et al. 2008).

Based on the controversies surrounding the utilisation of Inspiratory Incentive Spirometry (IIS) and Expiratory Incentive Spirometry (EIS) in the management of respiratory impairments, our study was conceived to compare the effect of inspiratory and expiratory incentive spirometry exercise on the pulmonary parameters and quality of life (QoL) of patients with obstructive, restrictive or mixed respiratory impairments and to determine the most suitable intervention for the respective respiratory impairments.

According to Parshall et al. (2012), respiratory impairment is typically established by conducting a pulmonary function test (PFT) using a spirometer and subsequently categorised as airflow limitation (e.g. COPD or asthma) or airflow restriction (e.g. interstitial lung disease or heart failure). The criteria that define this airflow limitation are based on the GOLD (Rabe et al. 2007).

Based on American Thoracic and European Respiratory Societies (ATS/ERS) performance guidelines for pulmonary function tests, a portable handheld device can be utilised for spirometry by instructing the participant to perform a series of forceful and complete exhalation manoeuvres, starting from maximal inspiration with the breathing manoeuvres generating two specific lung volumes, namely the FVC (an untimed lung volume) and FEV_1_ (a timed lung volume) (Pellegrino et al. 2005).

In managing respiratory diseases, a lack of awareness, knowledge and often delay in recognition of the disease is one of the reasons why primary care practitioners and other healthcare providers may incorrectly diagnose or manage the condition (Yawn & Wollan 2008). The pulmonary function test is a simple and accurate tool to assess airflow obstruction. Patients FEV_1_/FVC ratio is reduced, and FEV_1_ is reduced in COPD (Gold & Koth 2015). An airway reversibility test differentiates COPD from asthma, as COPD patients do not show reversibility in airflow obstruction after administration of bronchodilators (Vestbo et al. 2013).

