### Sample size calculation

The pulmonary function test is the primary outcome of interest for our study and the expected clinically relevant difference for obstructive restrictive and mixed impairment using LLN and GLI reference equation as proposed by Quanjer et al. (1993). Therefore, the sample size (*n*) will be determined using G-Power statistics software (stats.oarc.ucla.edu). The power is selected at 95% = 0.95, confidence level at 5% = 0.05 and effect size of 0.35 (Figure 1), namely:

**F-tests – MANOVA:** Repeated measures, within-between interaction

**Options:** Pillai V, O’Brien-Shieh Algorithm

**Analysis:** A priori: Compute required sample size

**Input:** Effect size f(V) = 0.35

    α err prob = 0.05

    Power (1-β err prob) = 0.8

    Number of groups = 9

    Number of measurements = 6

**Output:** Non-centrality parameter λ = 31.2375000

     Critical F = 1.4522092

     Numerator degree of freedom (*df*) = 40.0000000

     Denominator df = 210

     Total sample size = 51

     Actual power = 0.8010637

     Pillai V = 0.5456570

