**FIGURE 1 F0001:**
[figure not shown]
F-test multivariate analysis of variance of within/between group interaction.

We intend to investigate the main effects, within and between interactions, for two factors, namely:

Factor A – Therapy with three levels (Therapy A, Therapy B and No Therapy)Factor B – Types of impairments (Obstructive, Restrictive and Mixed) nested within factor A

This gives 3 × 3 = 9 groups of participants from which repeated measurements are to be obtained.

We are also planning to measure three continuous outcomes at different time points of which the minimum repeated measurements are expected to be six per subject for some of the outcomes and a maximum of 36 per subject. Suppose a minimum of six repeated measures is to be obtained from each subject, in that case, it is estimated that a minimum total sample size of 51 patients is required to detect an effect size v = 0.35 with 95% confidence (5% Type I) – similar studies also expected to produce similar results about 80% of the time (Power of test 80%). In the case that during the time of data collection, the hospital experiences a high number of COPD, IPF, ILD, cystic fibrosis, thoracic cage abnormalities patients or resources permit, we are able to increase the total sample size to at most 68 subjects with a corresponding increase in the power of the test to about 95% still detecting effect sizes between 0.3 and 0.4 (see Figure 1). This translates to the possibility of recruiting between five and eight patients per group. Hence, the sample size estimates suggest that recruiting more than eight patients per group for our study will be a waste of resources.

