### Data analysis

The Statistical Package for Social Sciences (SPSS Inc, Chicago, Illinois, United Sates) version 26.0 for windows package programme will be used to analyse data. Descriptive statistics of mean, standard deviation, frequencies and percentages will be used to summarise the results. Bar charts, pie charts and histograms will be utilised for pictorial illustration. A multivariate analysis of variance (MANOVA) will be used to compare the outcome pulmonary function variables (FEV_1_, FVC, FEV_1_/FVC, PEFR) and QoL (6MWT, MRC dyspnoea scale score and PFSDQ-M score) among groups, while the Bonforreni’s *t*-test will be utilised for post hoc analysis to detect where significant changes occurred in the outcome variables. Dependent t-tests will be used to compare the pre- and post-test results within variables while independent t-tests will be used to compare the outcome variable among the study and control groups. The level of significance will be set at *p* ≤ 0.05.

The study does not potentially involve risk or harm, as all interventions can only be performed within the limit of the patient’s tolerance. However, participants may experience mild discomfort because of the exercise, including temporary muscle soreness, increased heart rate, blood pressure, sweating and dizziness. All necessary care will be in place to prevent the occurrence of any adverse event. However, in case of a report of serious adverse events (e.g. comorbidities, injuries, persistent excruciating pain, dizzy spells, headache, etc.) after the intervention or at any point during the trial, we would consider unblinding the participant to the intervention for their safety. Additionally, the participants will be instructed to report adverse events to the first author PI or the physiotherapist supervising their group. To ensure adequate supervision, participants per group to be attended in a day will be limited to a maximum of three. Arrangements will be made with the Accident and Emergency units of the research site to provide a standby medical team. The University of KwaZulu-Natal insurance scheme on clinical trials has fully covered participants in this type of study.

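### Impairment class is specified as nested within therapy, so the therapy-by-class test that class-specific advice needs is neither defined nor separately powered

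*Protocol article*

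**What the plan says.** **Purpose.** The Background section of the protocol article compares IIS with EIS in obstructive, restrictive and mixed impairment, and wants "to determine the most suitable intervention for the respective respiratory impairments".

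**Design.** The Abstract groups 54 patients by impairment class, 18 per class, and divides each class into three groups of six. The section on randomisation and blinding also allocates by class and then into subgroups.

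**Model.** The text after Figure 1, in the sample size section, says that main effects and interactions for two factors will be investigated. Factor A is therapy, with three levels. Factor B is given as "Types of impairments (Obstructive, Restrictive and Mixed) nested within factor A". The same text multiplies three by three to obtain nine groups.

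**Sizing.** The calculation is a MANOVA of the type "Repeated measures, within-between interaction", with "Effect size f(V) = 0.35", "α err prob = 0.05", "Power (1-β err prob) = 0.8", nine groups and six measurements. It gives a total of 51.

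**Analysis.** The Data analysis section plans a MANOVA among groups. Bonferroni t-tests "will be utilised for post hoc analysis to detect where significant changes occurred in the outcome variables". Dependent t-tests compare pre with post, and independent t-tests compare study with control groups. No test of therapy by class, with or without time, is named.

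**The concern.** The statement that IIS suits one class and EIS another says that the IIS-EIS difference changes with class. That is a therapy-by-class interaction, or therapy-by-class-by-time in a repeated-measures model. A significant result in one class and a non-significant one in another does not show that the classes differ.

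The document names the ingredients (two factors, interactions) but describes a structure from which this interaction is absent. The same three classes occur under every therapy, so the factors are crossed. If class is fitted as nested, class and interaction are merged into one term. Patients are sorted into classes by their FVC and FEV1/FVC, so large class differences in those outcomes exist by construction and would tend to dominate the merged term when outcome levels are analysed.

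At stake is the basis for class-specific advice, which the Discussion section hopes will enter clinical guidelines. Without the interaction term, such advice would have to rest on patterns among comparisons of very small cells.

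**Working it through.** **1. The plan's own figure.** With k = 9 groups, m = 6 measurements, N = 51 and s = min(k − 1, m − 1) = 5:
- numerator df = 8 × 5 = 40
- denominator df = 5 × (51 − 9 − 5 + 5) = 210
- λ = 51 × 5 × 0.35² = 31.2375
- critical F = 1.4522; power = 0.8011

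These match the document, so the calculation is reproduced. (A sentence above it says "The power is selected at 95% = 0.95", but the input was 0.8. That is a separate inconsistency.)

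**2. What that test contains.** It has 8 df between groups and 5 for time. With crossed factors the 8 df split into therapy 2, class 2 and therapy-by-class 4. By time, the 40 df split into 10 + 10 + 20. The sized test merges all three parts.

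**3. What nesting does.** Class within therapy has 3 × (3 − 1) = 6 df. This equals 2 df of class plus 4 df of interaction. No 4-df term is left to test.

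**4. Disagreement between classes when the true effect is the same in each.** Assume an identical IIS-EIS difference of d SD in all three classes, tested 6 v 6 (10 df) in each. If p is the power in one class, the chance that one or two of the three are significant is 1 − p³ − (1 − p)³. The values of d are assumptions, and so is the Bonferroni family, which the document does not state: 3 comparisons (α = 0.0167) or all 36 pairs of nine cells (α = 0.0014).

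| d (SD) | p, uncorrected | Disagree, uncorrected | Disagree, family of 3 | Disagree, family of 36 |
|---|---|---|---|---|
| 0.5 | 0.123 | 32% | about 15% | 2% |
| 0.8 | 0.241 | 55% | 31% | 5% |
| 1.0 | 0.347 | 68% | 45% | 9% |
| 1.5 | 0.650 | 68% | 74% | 30% |

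Example at 0.8 SD, uncorrected: 1 − 0.241³ − 0.759³ = 1 − 0.014 − 0.437 = 0.549. The formula peaks at 75% when p = 0.5, near d = 1.2 uncorrected.

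**5. Precision of the contrast that is needed.** Take one outcome at one time point, and the IIS-EIS difference in one class minus that in another. Four cell means of six patients give SE = √(4/6) = 0.816 SD. With 54 − 9 = 45 df, t = 2.014, so the 95% half-width is 2.014 × 0.816 = 1.64 SD. Power is 0.22 for a true difference of 1 SD and 0.67 for 2 SD. About 2.3 SD is needed for 80%.

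**The case against.** A reader might infer that the trial never tests interaction and only inspects cells one at a time. The documents do not support that. Interactions for the two factors are announced, the analysis opens with an omnibus MANOVA, the post hoc tests carry a Bonferroni correction, and the independent t-tests are not said to be run within class. The word nested may be loose drafting, since the nine-group layout beside it is crossed. All of this stands. It makes the defect a wrong model statement and an unnamed test, not a decision against testing.

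A reader might also infer that a therapy which works equally in all classes will usually look class-specific. That is not supported either. Even uncorrected, disagreement is 32% at 0.5 SD, and under a wide Bonferroni family it stays at 30% or less at every effect size shown. It becomes an error only if it is read as a class difference, and the document states no such rule.

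Three further points have some weight:
- **Simple effects.** Which device is better in each class can be asked within each class. That is true, but saying that the answer differs between classes needs the interaction. A 6 v 6 comparison at 0.05 needs about 1.80 SD for 80% power.
- **Prominence.** The formal aim and the two objectives contain no ranking by class, and the clinical implication is hedged. The class-specific purpose is nevertheless stated in the Background section.
- **Condensed article.** A full analysis plan may define the contrasts, so the missing test name alone would be a weak point. The nested specification, however, is a statement in this document that contradicts its own design.

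Finally, the power figure in step 5 is for one outcome at one time point. If f(V) = 0.35 were assumed for the therapy-by-class-by-time term itself at N = 54, then df = 20 and 176, λ = 54 × 4 × 0.35² = 26.46, and power is 0.87. The document justifies no such value for that term.

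**Conclusion.** The point holds in this form: the protocol article announces interactions but specifies class as nested within therapy, against its own crossed layout. Followed as written, the model has no therapy-by-class term, the sized 40-df test does not isolate one, and no listed test supplies one. The plan therefore cannot support different advice for different classes.

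The size of the risk depends on assumptions. With six per cell and equal true effects, disagreement in significance is 32% to 68% at the four uncorrected values between 0.5 and 1.5 SD. Under Bonferroni it is about 15% to 74% for a family of 3 and 2% to 30% for a family of 36, and correction does not lower it at 1.5 SD for the family of 3. The limit on precision does not depend on the correction: a half-width of about 1.6 SD and 22% power for a 1 SD between-class difference, assuming a common SD, no dropout, and one outcome at one time point.

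**What to change.** - In the text after Figure 1, describe therapy and impairment class as crossed factors instead of nested ones.
- In the Data analysis section, name the therapy-by-class term (4 df), by time in the repeated-measures model, as the test for class-specific conclusions.
- State that the devices differ in suitability between classes only if that term is shown. Otherwise report the therapy effect averaged over classes as the conclusion, and give per-class IIS-EIS estimates with confidence intervals as exploratory.

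This needs no more patients, visits or measurements, only changes to the model statement and the wording of conclusions. The price is that class-specific rankings will rarely be supportable at six per cell, and the report would have to say so.

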## Significance of our study

The outcome of our study may establish the relationship between inspiratory and expiratory types of incentive spirometry in the management of obstructive, restrictive and mixed respiratory impairments.

Although studies have identified the general effect of incentive spirometry (IIS and EIS) in the management of respiratory conditions, none has been able to exclusively compare the impact of IIS with EIS on the different classes of respiratory impairments, thereby limiting the opportunity to identify the most suitable treatment modality for respiratory impairments. Our study is therefore designed to answer the following question.

What will be the effect of inspiratory and expiratory incentive spirometry on pulmonary function test (PFT), six-minute walk test (6MWT), Medical Research Council (MRC) dyspnoea scale and the Pulmonary Function Status and Disability Questionnaire-modified (PFSDQ-M) on patients with obstructive, restrictive or mixed respiratory impairments?

Thus, the aim of our study is to determine the effect of inspiratory and expiratory type of incentive spirometry on PFT, 6MWT, MRC dyspnoea scale score and PFSDQ-M score of patients with obstructive, restrictive or mixed respiratory impairments.

The specific objectives of our study are to determine:

The effect of inspiratory incentive spirometry on FEV_1_, FVC, FEV_1_/FVC, PEFR, 6MWT, MRC dyspnoea scale score and PFSDQ-M score of patients with obstructive, restrictive or mixed respiratory impairments.The effect of expiratory incentive spirometry on FEV_1_, FVC, FEV1/FVC, PEFR, 6MWT, MRC dyspnoea scale score and PFSDQ-M score of patients with obstructive, restrictive or mixed respiratory impairments.

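### The trial is motivated by comparing IIS with EIS within each impairment class, but no objective, named contrast or sample size addresses that comparison

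*Protocol article*

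**What the plan says.** **Purpose.** The Background says the study was conceived to compare the two therapies and "to determine the most suitable intervention for the respective respiratory impairments". Significance of our study gives the gap in earlier work: "none has been able to exclusively compare the impact of IIS with EIS on the different classes of respiratory impairments". The Abstract's Clinical implication says the results may indicate whether "inspiratory incentive spirometry or expiratory incentive spirometry is better suited for the treatment of the respiratory impairment".

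**Objectives.** In Significance of our study, the research question and the aim ask for the effect of the two types of spirometry. The list that begins "The specific objectives of our study are to determine" has two items: "The effect of inspiratory incentive spirometry on FEV_1_, FVC, FEV_1_/FVC, PEFR, 6MWT, MRC dyspnoea scale score and PFSDQ-M score of patients with" the three impairment types, and "The effect of expiratory incentive spirometry on FEV_1_, FVC, FEV1/FVC, PEFR, 6MWT, MRC dyspnoea scale score and PFSDQ-M score of patients with" the same. Neither names a comparator, and there is no third item.

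**Analysis.** Data analysis plans a MANOVA among groups, a Bonferroni post hoc t-test to find where changes occurred, dependent t-tests before and after, and a last step in which "independent t-tests will be used to compare the outcome variable among the study and control groups". The set of comparisons covered by the Bonferroni step is not given.

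**Size.** Sample size calculation uses the repeated-measures MANOVA within-between interaction with nine groups and six measurements, and gives a total of 51. The Abstract plans 54: three classes of 18, each split into three groups of six.

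**The concern.** The document states its purpose and its objectives, and they do not match. The purpose is a difference between two active therapies, by class. The objectives are two separate effects. The analysis section lists its tests but gives no estimate of the IIS-EIS difference and no confidence interval for it.

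An omnibus test over nine groups can be significant for many reasons and gives no direction for IIS against EIS. Finding one therapy significant against control and the other not does not test one against the other. The trial could therefore end without an estimate of the quantity it was set up to obtain. The stated power of 80% also says nothing about that quantity, so readers may think the comparison is better supported than it is.

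**Working it through.** **1. Reproduce the stated figure.** Inputs from Sample size calculation: f(V) = 0.35, alpha 0.05, 9 groups, 6 measurements, N = 51.
- s = min(9 − 1, 6 − 1) = 5
- numerator df = 8 × 5 = 40
- denominator df = s(N − 9 − 5 + s) = 5 × (51 − 9 − 5 + 5) = 210
- λ = N × s × f² = 51 × 5 × 0.1225 = 31.2375
- critical F = 1.4522; power = 0.801

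This matches the document, and N = 50 gives 0.789, so 51 is the minimum. The planned 54 gives 0.835. All of this concerns the 40-df interaction, not any pairwise difference.

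**2. Size of the IIS-EIS comparison.**
- Within one class: 6 v 6 (Abstract, Method).
- Pooled over the three classes: 3 × 6 = 18 v 18.
- Pooled error df = 54 − 9 = 45.
- Possible Bonferroni families: all cell pairs, 9 × 8 / 2 = 36; or the three therapy levels, 3 × 2 / 2 = 3. The document states neither.

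**3. Power for one two-sided contrast.** Noncentral t with noncentrality d × √(n/2) and 45 df. Here d is the difference in units of the within-cell SD of the analysed outcome. The document gives no pairwise effect or SD, so d is an assumption and is shown over a range.

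| Comparison | Alpha | d = 0.5 | d = 0.8 | d = 1.0 | d for 80% power |
|---|---|---|---|---|---|
| One class, 6 v 6 | 0.05/36 | 0.9% | 3.0% | 5.9% | 2.47 |
| One class, 6 v 6 | 0.05/3 | 6% | 15% | 24% | 1.93 |
| One class, 6 v 6 | 0.05 | 13% | 27% | 40% | 1.65 |
| Pooled, 18 v 18 | 0.05/3 | 17% | 47% | 70% | 1.11 |
| Pooled, 18 v 18 | 0.05 | 31% | 65% | 84% | 0.95 |

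Example, first row at d = 1.0: noncentrality = 1.0 × √3 = 1.732, alpha = 0.00139, critical t = 3.41, power 5.9%. At the upper limit of eight per group given in Sample size calculation (8 v 8, 63 df, alpha 0.05/36), power at d = 1.0 is about 10%.

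**4. Precision within a class.** The unadjusted 95% CI half-width is t × √(2/n) = 2.014 × √(2/6) = 1.16 SD for 6 v 6, and 2.014 × √(2/18) = 0.67 SD pooled.

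**5. What pooling can hide.** If IIS and EIS differ by 1.0 SD in one class and not in the other two, the pooled difference is (1.0 + 0 + 0)/3 = 0.33 SD. Noncentrality = 0.333 × √9 = 1.0, and power at 0.05 is about 16%.

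**The case against.** The strongest reply is that the comparison is not missing from the analysis. The MANOVA includes both active arms, the post hoc step follows it, and the phrase about study and control groups is loose enough to cover IIS against EIS. This is also a condensed article with no analysis plan shown, so details of contrasts may sit elsewhere. That stands as far as it goes: the analysis can reach the comparison. It does not explain why the article's own question, aim and objectives omit the purpose that the article itself states.

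Several stronger readings are tempting but not supported:
- **That the plan is a 36-pair search.** That number follows from nine cells, but Data analysis states no family. The sample size section describes therapy as a three-level factor with main effects, so three pairs is equally open.
- **That the trial has almost no chance of detecting a difference.** This holds for a class-specific contrast corrected over 36 pairs with d up to about 1. It does not hold for the pooled contrast, which has 47% power at 0.8 SD and 70% at 1.0 SD with three pairs.
- **That planning the contrast lifts power from 6% to 84%.** Those two figures differ in the question asked, in n and in alpha. Within a class, dropping all adjustment raises power only from 6% to 40%.
- **That the investigators will infer a winner by comparing two significance results against control.** The plan leaves room for this, but nowhere says it.

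A fair further point is that a pooled contrast alone would replace the class-specific question with another one. Step 5 of the working shows why it cannot stand in for the class-level differences.

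**Conclusion.** The point holds as a mismatch between purpose and plan, and needs no power figure to stand. The article's stated purpose is IIS against EIS by class; its objectives do not ask for it, no named contrast estimates it, and its sample size is for something else.

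On size, six per group is too few for a class-specific answer under any of the adjustments considered: 80% power needs differences of 1.65 to 2.47 SD. The pooled comparison is better placed, at 1.11 SD with three therapy pairs or 0.95 SD as a single test, but it answers which therapy is better on average, not which suits each class. These figures assume two-sided tests, complete data on 54 participants, a common SD with 45 error df, and effect sizes that the document does not supply. Baseline adjustment would shrink the relevant SD by an amount the document does not allow one to estimate.

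**What to change.** 1. Add a third specific objective: the IIS-minus-EIS difference in each outcome, overall and by impairment class.
2. In Data analysis, pre-specify it as a planned contrast in the therapy-by-class model, adjusted for baseline, at a stated time point, with a 95% CI.
3. Report the pooled difference and the three class-specific differences with their CIs side by side. State that six per group gives the class-specific differences only exploratory precision, and that the pooled contrast does not by itself show which therapy suits each class.
4. State the Bonferroni family and limit it to the three therapy pairs. Quote the power that goes with that alpha (70% at an assumed 1.0 SD; 80% at 1.11 SD), not the figure for a single test at 0.05.

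The cost is protocol wording; no extra participants or measurements are needed. The downside is that recommendations by impairment class must be worded as exploratory, which limits the claim made in the Abstract's Clinical implication.
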